##### Provider credentials

2.6.1.3

(1) Steering group: Comprises physicians with attending physician or higher professional titles (with extensive clinical experience) and registered nurses with a bachelor’s degree and ≥5 years of work experience (proficient in communication). Psychotherapists are also included to support training and content development.(2) Peer educators: PPD patients meeting the following criteria: (i) cheerful personality with strong communication and organizational skills; (ii) high motivation and sense of responsibility; (iii) high school education or above, proficient in using smartphones; (iv) demonstrated effective postpartum depression self-management. They must pass a post-training assessment on health knowledge to qualify.

##### Methods of intervention delivery

2.6.1.4

(1) All interventions are delivered online via WeChat, including;(2) Asynchronous content sharing (articles, videos) in designated groups Synchronous video group chats (weekly) for interactive discussions.(3) Bidirectional feedback: Peer educators regularly report to the steering group on group dynamics and content effectiveness, enabling real-time adjustments.

##### Intervention schedule

2.6.1.5

(1) Training phase: 2 weeks, with 3 sessions/week (2 h/session) for peer educator training (group training and individual counseling).(2) Intervention phase: 6 weeks, with: Weekly sharing of educational articles/videos by peer educators.(3) One weekly video group chat (duration not specified, but structured to address self-management issues and experience sharing).

#### Competency assessment of peer educators

2.6.2

The competency assessment of peer educators is primarily conducted across six dimensions: knowledge proficiency, communication and guidance skills, organizational and coordination capabilities, problem-solving abilities, sense of responsibility and execution, and professional competence. Detailed evaluation criteria are specified in the Supplementary materials
**“**Competency Assessment of Peer Educators.” A 100-point scoring system is employed to quantify peer educators’ competencies, with performance indicators weighted as follows: knowledge proficiency accounts for 30%, communication and guidance skills for 25%, organizational and coordination capabilities for 15%, problem-solving abilities for 15%, sense of responsibility and execution for 10%, and professional competence for 5%. A total score of 80 points or above indicates competency qualification for peer educator responsibilities; scores between 60 and 79 points signify the need for targeted retraining; scores below 60 points denote disqualification from peer educator roles.

#### Process evaluation plan

2.6.3

##### Qualitative tools

2.6.3.1

###### Outline of semi-structured interview (for peer educators)

2.6.3.1.1

(1) Basic information: including the duration of peer education work, the specific time of participating in this project, etc.(2) Interaction Effects: “What were the three most effective moments in your group interaction this week? Describe the situation and why in detail.” “What is the biggest communication barrier you have faced when guiding group members to communicate? What coping strategies did you try? How did it work?”(3) Personal feelings: “In the process of peer education, what links make you feel a sense of achievement? What aspects of peer education make you feel stressed?” “Do you think your current abilities are well suited to the role of peer educator? If so, what are the main areas of weakness?”

###### Focus group discussion guide (for subjects)

2.6.3.1.2

(1) Activity format Acceptance: “How satisfied are you overall with the current activity format within the group? Explain why.” “What forms of activity do you wish to add or adjust? Why?”(2) Feeling of Content: “What content does the group share that makes you feel understood and supported? Give an example.” “Is there any content that makes you feel offended or uncomfortable? What was it, specifically? Why do you feel this way?”(3) Engage in motivation: “What makes you want to engage in group interactions and activities?” “What factors decrease your motivation to participate?”

###### Guide template for electronic reflection diary (for both parties)

2.6.3.1.3

Daily Diary: “What was the one thing that impressed you most about your in-group communication today? How did it make you feel?” “Did you take the initiative to speak or participate in the group today? If not, what is the reason?”

Weekly summary: “What have you learned or learned from your learning and interaction in the group this week?” “How did you feel about the interaction in the group this week? What can you improve on?”

###### Anonymous feedback box (online)

2.6.3.1.4

Set up a simple feedback entrance, suggesting the direction of the content of feedback, such as “I have thoughts on the speech of a member of the group,” “I feel that a certain activity is unreasonable,” “I have any other suggestions or complaints about the interaction in the group,” etc., and the feedback form is not limited, such as text and voice.

##### Time node of data collection

2.6.3.2

(1) First assessment: 1 week after the intervention, participants had initially adapted to the group environment and interaction mode, and could provide some valuable feedback, mainly to understand the initial acceptability and participation.(2) Stage evaluation: the intervention was carried out at the third and sixth week, and the changes of acceptability, participation and negative dynamics were tracked through multiple assessments in the process of intervention, so as to find and adjust problems in time.(3) Summative evaluation: after the intervention, the feedback of the whole intervention process was collected comprehensively, the effectiveness, existing problems and improvements of the intervention were summarized, and the experience reference for subsequent related interventions was provided.(4) Collect in real time: an electronic reflection diary encourages both parties to submit at a fixed time daily or weekly; Anonymous feedback boxes support participants to submit feedback at any time, ensuring that emergent feelings and questions are captured in a timely manner.

##### Data analysis methods

2.6.3.3

(1) Data collation: arrange special personnel to transcribe semi-structured interview recordings and focus group discussion recordings into text data in time, classify and sort out the contents of electronic reflection diary and anonymous feedback box to remove duplicate or invalid information and ensure the completeness and accuracy of data.(2) Coding and theme extraction: Thematic analysis was used by two independent psychotherapists. First of all, they read all the materials and were familiar with the content. After open coding, meaningful sentences and paragraphs were marked with different concepts. Then axis coding was performed to classify related concepts into sub-themes. Finally, selection coding was carried out to extract three core themes of “acceptability,” “participation” and “negative dynamics” and their specific subthemes.(3) Consistency test: after the two psychotherapists finished coding, the coding consistency coefficient was calculated. If the coefficient was lower than 0.8, the differences were discussed together, and the final coding result was determined after reaching a consensus to ensure the reliability of the analysis.(4) Results presentation and application: According to the coding results, the process evaluation brief was formed, and the specific performance and occurrence frequency of each theme were elaborated in detail. The brief was presented to the steering group, which adapted the intervention based on the intervention objectives and the actual situation. For example, if there is a lot of feedback in the “acceptability” theme about “the weekly theme task challenge is too difficult,” reduce the difficulty of the task; If “anxiety caused by the comparison of parenting experience among members” appeared frequently in the “negative dynamic,” the relevant activity links would be adjusted.

#### Quality control

2.6.4

##### Double-track system of content review

2.6.4.1

A strict double-track system of content review is established. All articles, videos and other materials to be shared in the group must be reviewed by both professional doctors and psychotherapists in the steering group. Focus on screening inappropriate expressions that may cause maternal anxiety, such as “you must adhere to exclusive breastfeeding, or you are an incompetent mother” and “you should quickly recover your figure after childbirth, or you will be rejected.”

##### Dynamic evaluation system

2.6.4.2

Build a comprehensive dynamic evaluation system, and use a simple and intuitive “emotional thermometer” scale (0–10 points) to quickly evaluate the members’ emotions every week. If the member’s score is ≥7, the peer educator should immediately conduct a 15-min private chat with the member to deeply understand the causes of his or her emotional fluctuations, and provide personalized psychological support and suggestions. The emotional trend of the group was summarized and analyzed every month, and a detailed emotional trend map was drawn. Based on the trend chart, the steering group was keen to judge whether the focus of education content needed to be adjusted. For example, if the score of “sleep disturbance” dimension was high for two consecutive weeks, the thematic content on postpartum sleep improvement should be added in time, including sleep environment construction and sharing of sleep AIDS.

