The secondary objective is to examine health related quality of life, the self-management ability and safety. We hypothesize, that the IPE group will lead to a significantly greater quality of life, better self-management and less adverse event than RHE group.

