### Randomization and allocation

2.4

The randomization was conducted using a computer-generated random number table (produced by SPSS 26.0 software) to ensure the unpredictability of group assignments. A total of 88 random numbers were generated, and each number was correspondingly assigned to either the intervention group (Internet-based peer education group) or the control group in a 1:1 ratio, with 44 subjects allocated to each group.

For allocation concealment, the research assistant who was not involved in subject recruitment prepared sequentially numbered opaque brown paper envelopes. Each envelope contained a card indicating the subject number, the generated random number, and the corresponding group assignment. These envelopes were sealed and stored in a locked cabinet to prevent premature disclosure.

When a qualified subject was enrolled, the researcher opened the envelopes in strict sequence according to the enrollment order (i.e., the first enrolled subject received the first envelope, the second subject the second envelope, and so on). The subject was then allocated to the group specified in the opened envelope. This procedure ensured that neither the researchers nor the subjects could predict the group assignment before enrollment, thus minimizing selection bias.

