##### Procedures

2.6.1.2

(1) Steering group establishment: A multidisciplinary team is formed to oversee intervention design, peer educator training, and quality assurance.(2) Peer educator selection and training: Eligible PPD patients are recruited, trained over 2 weeks, and assessed for competence before participation.(3) Group formation: Enrolled subjects are assigned to WeChat education groups (maximum 11 subjects per group) containing steering group members, peer educators, and participants.(4) Intervention implementation: Under the leadership of the guidance team, peer educators are trained and supervised to implement interventions for the subjects. The intervention measures include:i. The guidance team disseminates curated postpartum dietary, exercise, and psychological adjustment content every Monday, Wednesday, and Friday, with a monthly communication plan;ii. Peer educators provide weekly updates on member dynamics and needs every Friday, with the guidance team responding and adjusting within two working days;iii. A 60–90 min group video chat is organized every Sunday evening, following an interactive process of “sharing—Q&A—summary”;vi. Peer educators focus on experience sharing, presenting emotional management case studies every Tuesday and Thursday, and conducting monthly thematic sessions (e.g., “Postpartum Sleep and Emotional Regulation”), fostering a supportive atmosphere through positive reinforcement to encourage subject participation and mutual assistance.(5) Safety protocol: Intervention is terminated immediately if participants exhibit suicidal tendencies or harmful behaviors, with referral to psychiatric care.

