### Statistical analysis plan

2.10

The statistical analysis will be conducted by independent statisticians who will be blinded to group allocation and intervention methods. Before data analysis, the research group will draw up a statistical plan, including the required data and method of data processing. For Categorical data, we performed the Chi-square (x^2^) test for between-group differences. For continuous and normally distributed data, we performed Student’s *t*-test for between-group differences and paired t test for within-group differences. If data were distributed nonnormally, the Mann–Whitney U test for between-group differences and the Wilcoxon test for within-group differences would be used. The normally distributed data were expressed as the mean ± standard deviation. Nonnormally distributed data would be expressed as the median or interquartile range (IQR). For categorical variables, the X^2^ test will be used to examine the between-group differences, and percentages and frequencies will be presented to describe the effect size.

For longitudinal data analysis considering the repeated measurements at assessment nodes in this study, the Generalized Estimating Equations (GEE) model will be employed.

Fixed effects structure: It will include the group variable (experimental vs. control), time points (six assessment nodes as a categorical variable), and the interaction term between group and time points. Additionally, potential confounding variables (e.g., baseline characteristics that show imbalance between groups) will be incorporated into the model as covariates to adjust for their effects.

Correlation structure: Given the repeated measurements within individuals over time, the exchangeable (compound symmetry) correlation structure will be initially assumed, which posits that the correlation between any two measurements from the same individual is equal. Sensitivity analyses will be conducted using other correlation structures (e.g., autoregressive of order one, which assumes a higher correlation between measurements that are closer in time) to assess the robustness of the results. The working correlation matrix will be estimated based on the observed data during model fitting.

All clinical data analyses will be performed using SPSS V.22.0 software. Missing data will be handled using the multiple imputation method. A two-tailed test will be conducted, and a *p* < 0.05 will be considered statistically significant.

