### Safety

2.13

The steering group members and the assessment researchers will closely observe the psychological conditions of the peer educators and the participants during the whole course of trial. If an adverse event (AE) happened during intervention, it would be assessed and recorded in the case report form (CRF). The relevant adverse events may include deterioration of the depression, aggravating hopelessness, anxiety and somatic symptoms (et al., dizzy, pain). Serious adverse events include self-harm tendency, suicide attempt, and injury-infant behavior. Once a serious adverse event occurs, the participant will be immediately terminated from this trial and will be referred to a psychiatric clinic as soon as possible.

In addition to routine exclusion and monitoring criteria for suicidality, specific measures for symptom emergence during non-usual clinic hours are established. Participants will be provided with a 24/7 emergency hotline connected to on-call psychiatric professionals. Upon reporting suicidal symptoms, the on-call team will conduct immediate risk assessment via phone, dispatch emergency services if necessary, and coordinate with the participant’s primary caregiver for in-person supervision until professional intervention is available. Documentation of all interactions and follow-up actions will be maintained in the participant’s record.

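### Adverse-event observation rests partly on steering-group members placed inside the IPE groups, so the hypothesised comparison of adverse events between arms is exposed to unequal detection

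*Protocol article*

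**What the plan says.** **The hypothesis.** The Introduction states: "The secondary objective is to examine health related quality of life, the self-management ability and safety". It goes on to expect "better self-management and less adverse event than RHE group". Section 2.10 names no adverse-event analysis, but its general rules would apply: "For Categorical data, we performed the Chi-square (x^2^) test for between-group differences", and "A two-tailed test will be conducted, and a *p* < 0.05 will be considered statistically significant".

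**Who observes.** Section 2.13 has both the steering-group members and the assessment researchers watch participants' psychological condition. The events it lists are mainly worsening depression, hopelessness, anxiety and somatic symptoms.

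**Where the steering group sits.** Section 2.6.1.2 places its members in the IPE WeChat groups and adds: "Peer educators provide weekly updates on member dynamics and needs every Friday". Section 2.6.1.4 names the steering group as the recipient of the peer educators' reports.

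**Further contact in IPE only.** Section 2.6.4.2 uses a 0–10 emotional thermometer to "quickly evaluate the members’ emotions every week", with a 15-minute private chat at 7 or above. Section 2.6.4.3 adds a steering-group telephone call after two consecutive absences.

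**What both arms share.** All participants receive RHE (Section 2.1), with the calls and outpatient interviews of Section 2.6.5. Table 1 lists adverse events at every assessment through T5.

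**Recording window.** Section 2.13 says: "If an adverse event (AE) happened during intervention, it would be assessed and recorded".

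**The concern.** Most of the listed events are changes in mood or symptoms that enter the record only if somebody asks or notices. If one arm has additional observers, more of its events will be found at the same true risk. The steering group delivers IPE and so knows the allocation of the women it observes, whereas Section 2.5 keeps the efficacy raters unaware of allocation.

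The likely bias runs against IPE. That does not make it harmless, because the question asked is whether IPE has fewer events. A true reduction could be hidden, or equal safety could look like harm from IPE.

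**Working it through.** The plan gives no adverse-event rate, detection rate or power for this comparison, so there is no figure to reproduce. The check is first a comparison of passages, then an illustration on assumed rates.

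**Step 1: routes by which an event could be noticed**

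| Route | IPE | RHE | Described as adverse-event collection? |
|---|---|---|---|
| Assessments T1–T5, blinded raters (2.5, 2.8, Table 1) | yes | yes | yes |
| RHE calls and outpatient interviews (2.6.5) | yes | yes | no |
| Emergency hotline (2.13) | yes | yes | no |
| Steering-group observation (2.13), from within the WeChat groups (2.6.1.2) | yes | no matching position described | yes, by 2.13 |
| Friday updates (2.6.1.2) | yes | none described | no |
| Thermometer and private chat (2.6.4.2) | yes | none described | no |
| Steering-group call after absences (2.6.4.3) | yes | none described | no |

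The fourth row carries the point. Section 2.13 makes the steering group an adverse-event observer, and the last three rows bring information about IPE members to the steering group or its peer educators.

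**Step 2: how much contact is shared**

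Over 6 weeks in each arm:
- RHE calls every 3 days for 14 days: 14 / 3 ≈ 4.7, so 4 to 5.
- RHE calls weekly for 4 weeks: 4.
- Outpatient interviews every 2 weeks: 6 / 2 = 3.
- Assessment calls at T1–T4: 4.
- Total: 15 to 16 live contacts.

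Detection in RHE is therefore far from absent. The asymmetry lies in the additional routes.

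**Step 3: illustration only, all rates assumed**

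Arm size is from Section 2.4: "with 44 subjects allocated to each group". Observed risk = true risk × detection probability. The test is the two-sided pooled two-proportion test at 0.05 (equivalent to chi-square), by normal approximation:

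P(significantly more with IPE) = 1 − Φ[(1.96·SE0 − d) / SE1], where d is the observed-risk difference (IPE − RHE), SE0 = √(2·p̄(1−p̄)/44) and SE1 = √((p1(1−p1) + p2(1−p2))/44).

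Worked case: true risk 30% in both arms, detection 60% RHE and 80% IPE. Observed risks are 0.30 × 0.60 = 0.18 and 0.30 × 0.80 = 0.24, so the risk ratio is 0.24 / 0.18 = 1.33. SE0 = 0.0868 and SE1 = 0.0866. (1.96 × 0.0868 − 0.06) / 0.0866 = 1.27, giving about 10% instead of 2.5%.

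| True risk RHE / IPE | Detection RHE / IPE | Observed RHE / IPE | Risk ratio | P(more with IPE) | P(fewer with IPE) |
|---|---|---|---|---|---|
| 20% / 20% | 60% / 80% | 12% / 16% | 1.33 | 7.8% | 0.6% |
| 40% / 40% | 60% / 95% | 24% / 38% | 1.58 | 29.2% | 0.0% |
| 20% / 20% | 80% / 95% | 16% / 19% | 1.19 | 5.6% | 1.0% |
| 40% / 40% | 80% / 95% | 32% / 38% | 1.19 | 8.5% | 0.5% |
| 40% / 20% | 60% / 60% | 24% / 12% | 0.50 | 0.0% | 30.8% |
| 40% / 20% | 60% / 80% | 24% / 16% | 0.67 | 0.2% | 15.2% |
| 40% / 20% | 60% / 95% | 24% / 19% | 0.79 | 0.6% | 8.2% |

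With equal detection and equal true risk, the risk ratio is 1.00 and each tail is 2.5%.

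**Step 4: the recording window, a separate matter**

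The intervention lasts 6 weeks. Recording only during it would omit 12 − 6 = 6 of 12 weeks if T5 is counted from the start of the intervention (Section 2.12), or 12 of 6 + 12 = 18 weeks if counted from its end (Section 2.8). Table 1 collects events through T5. This conflict touches both arms alike and adds nothing to the detection argument.

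**The case against.** A reader might infer that the thermometer, diaries and feedback box screen for adverse events in one arm only. The documents do not say so. The thermometer is a quality-control tool, and no passage makes a score of 7 or more an adverse event. Diaries and the feedback box are process-evaluation tools analysed for themes, and the box is anonymous. The link to adverse events is the role that Section 2.13 gives the steering group, and that sentence covers participants in general.

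A reader might also infer that removals after detected events would make loss of the week-6 primary outcome differ by arm. Section 2.13 ties removal from the trial to serious events only, and nothing indicates how often these would come to light solely through IPE. That inference is unsupported.

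It is fair to add that shared contact is dense, that Table 1 already provides a symmetric source, that the test is inferred from a hypothesis and a general rule, and that power is low anyway: about 31% for a true halving at equal 60% detection. These points limit the size of the problem. They do not remove it, because nothing confines the comparison to the symmetric source and Section 2.13 explicitly adds one embedded in a single arm.

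Finally, setting IPE-detected events aside could conceal harm from IPE itself, such as the anxiety from comparing parenting experience foreseen in Section 2.6.3.3. That objection stands, and it shapes the fix.

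**Conclusion.** The concern holds in limited form. As written, adverse-event observation is unequal between arms and partly unblinded, for event types that depend on being noticed, while fewer events with IPE is a stated hypothesis. The likely direction is against IPE.

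The size cannot be derived from the documents. Over the assumed range with equal true risks of 20–40%, the chance of a false finding of more events with IPE would be about 8–29% when detection is 60% in RHE and 80–95% in IPE, and about 6–9% at 80% against 95%. These figures show what unequal detection could do and do not estimate what it will do. The discrepancy over the recording window is real but separate.

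**What to change.** 1. State that the between-arm adverse-event comparison uses events elicited with the same questions by the blinded assessors at T1–T5 in both arms.
2. Add a source-of-detection field to the CRF.
3. Report all adverse events from any source by arm. Identify those found only through IPE channels, and leave them out of the between-arm test but not out of the safety report.
4. Reconcile the recording window in Section 2.13 with Table 1 so that one observation period applies throughout.

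The cost is small: an analysis sentence, a CRF field, a common set of questions and a wording correction. Some IPE-detected events will be reported but not compared, and item 3 keeps them visible. For visits already completed, the source of an event may have to be recovered from existing records where possible.
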